### Provisions for post-trial care {30}

Not applicable. All intervention components are validated and standardized procedures where no particular hazard is to be assumed. Additionally, an insurance is provided to all participants during the period of study participation.

### Outcomes {12}

As the primary outcome, the decrease in CaF after intervention (T1) measured by FES-I score in comparison to the SCG will be confirmed. All secondary outcome measures will be assessed at three time points (T0, T1, and T2) and changes between groups over time will be explored. Therefore, sarcopenia will be assessed by BIA, physical function will be tested by SPPB, and handgrip strength and physical activity will be tested by actigraphy. The VAS scale of EQ-5D will determine health-related quality of life. General psychological status will be explored with questionnaires for depression (GDS), perceived stress (PSS), and anxiety (GAS). Furthermore, MMSE and TMT A and B will determine cognitive function.

Pathophysiological parameters changes will be explored in blood samples such as levels of CRP, IL-6, TNF-alpha, and IL-10 for systemic inflammatory processes as well as gene expression of IL-1beta, IL-6, IL-10, and I-kappa B for intracellular inflammatory activity. In addition, stress system activity will be measured by changes in cortisol and alpha-amylase levels in salivary samples.

If a fall or accident resulting in severe injuries (e.g., fractures) occurs during the intervention period, it poses a potential risk to the participants and is therefore considered an adverse outcome.

### Participant timeline {13}

The participant timeline is shown in Table 4.

**Table 4 Tab4:**
[figure not shown]
The participant time line for the schedule of enrolment, interventions and assessments

*MMSE* Mini Mental State Examination, *BIA* Bioelectrical impedance analysis, *SPPB* Short Physical Performance Battery, *CaF* Concerns about falling, *TMT* Trail Making Test, *VAS* Visual analogue scale, *FES-I* Falls Efficacy Scale-International Version, *FES-IAB* FES-I Avoidance Behavior, *UP-COF* Updated perceived control of falling, *GDS* Geriatric Depression Scale, *PSS* Perceived Stress Scale, *GAS* Geriatric Anxiety Scale, *CRP* C-reactive protein, *IL-6* Interleukin 6, *TNF-α* Tumor necrosis factor α, *IL-1β* Interleukin 1β

### Sample size {14}

Calculation of optimal sample size is based on two sets of available information. First, the required sample size for successful reduction of CaF was computed, and second, the required sample size for reduction of inflammatory markers in consequence of successful interventions was computed.

The authors are rather confident with regard to reduction of CaF: Based on previous intervention studies using similar procedures [54–56], a small-to-medium effect of around *f* = 0.15 is expected for reduction of CaF (indicated by FES-I). A priori power analyses using G-POWER (3.1.9.2.) assuming a statistical power of 0.95 and alpha error probability of 0.05 (assumed correlation among repeated measures of 0.50, and non-sphericity criterion ϵ set to 1). This indicates that *n* = 154 participants will need to be enrolled to achieve a successful reduction of CaF. Based on a drop-out rate of about 25–30% [56], *n* = 200 participants need to be randomly assigned to a group (i.e., *n* = 100 per group).

Second, if CaF are successfully reduced in the intervention group, it needs to be determined if the computed sample size of *n* = 100 per group is sufficient to detect the hypothesized cross-sectional and prospective associations of CaF with stress system activity and inflammation. As there are no published studies regarding this main prediction, the assumptions are estimated based on preliminary findings and expectations by the authors of what constitutes an acceptable effect size. Previous unpublished data for cross-sectional association of FES-I with IL-6 revealed that a sample size of *n* = 63 (assuming a statistical power of 0.95 and alpha error probability of 0.05) would be required to find a moderate-to-large effect (*r* = . 4); this also remains for multiple linear regression with up to six predictors (requiring *n* = 75). It can be concluded that the estimated sample size enrolling *n* = 200 participants with a drop-out of 25–30% will yield a sufficient final participant number to not only successfully reduce CaF but also to find the hypothesized associations using bivariate correlation and multiple linear regression analyses. Support of this finding comes from a study showing that frequent aerobic exercise training had a medium-to-large effect with regard to reducing inflammatory mediators [62]. It should be noted that this study employed a more frequent (three times/week) and longer intervention (10 months) than planned in our study; therefore, we do expect a smaller effect.

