### Methods in analysis to handle protocol non-adherence and any statistical methods to handle missing data {20c}

Statistical analysis will be conducted with participants who adhere to the intervention, while non-adherent participants will be excluded from the analysis. Adherence to the intervention will be monitored at each session. Participants will be considered “adherent” to the intervention if they attend at least 15 sessions (75%). A drop-out rate of 25% was considered in the power calculation; therefore, per-protocol analysis will be conducted.

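### Randomising 200 with 25–30% dropout leaves fewer than the 154 the plan requires, and for the T0–T1 primary comparison f = 0.15 is a 0.60 SD between-arm difference that the small-to-medium label understates

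*Protocol article*

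**What the plan says.** All the inputs are in the protocol article, Sample size {14}. The effect is described as "a small-to-medium effect of around *f* = 0.15 is expected for reduction of CaF". Power is set at 0.95 with alpha at 0.05. The calculation is of the repeated-measures kind, with "assumed correlation among repeated measures of 0.50" as one input and the sphericity epsilon fixed at 1 as another. The result is "This indicates that *n* = 154 participants will need to be enrolled to achieve a successful reduction of CaF". The section then cites a dropout of about 25–30% and sets 200 to be randomised, 100 per arm.

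It does not name the F test (interaction, within or between), the number of groups or the number of measurements entered in G*Power. It gives no equivalent in FES-I points or SD units.

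Two other sections bear on this. Outcomes {12} defines the primary outcome: "the decrease in CaF after intervention (T1) measured by FES-I score in comparison to the SCG will be confirmed". The section on non-adherence and missing data {20c} says "A drop-out rate of 25% was considered in the power calculation" and restricts the analysis to adherent participants.

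**The concern.** There are two problems, and both concern what the trial can show on its primary outcome.

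First, the planned number does not deliver the stated requirement after the plan's own dropout, and two sections describe that dropout differently.

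Second, the effect size is given only as Cohen's f from a repeated-measures calculation. On that scale 0.15 sounds modest. For a two-arm comparison of change from T0 to T1, however, the calculation uses the number of measurements and the correlation as well as f, and the between-arm difference it corresponds to is considerably larger than the label suggests. A reader who takes the trial to have about 95% power for a small-to-medium standardised difference could give a null primary result more weight than it can bear.

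**Working it through.** **Inputs.** From Sample size {14}: f = 0.15, alpha 0.05, power 0.95, correlation ρ = 0.50, epsilon 1, dropout 25–30%, 200 randomised. From Trial design {8}: two arms, 1:1. From Outcomes {12}: the primary comparison is the FES-I decrease at T1, hence two measurements (T0, T1). This last input is inferred, because the sample-size section does not state it. Study procedure {11a} gives three time points for the trial as a whole.

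**Step 1: the plan's 154.** For the G*Power group-by-time interaction with k groups and m measurements, the noncentrality is λ = f²·N·m/(1 − ρ), with (k − 1)(m − 1) and (N − k)(m − 1) degrees of freedom.

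- m = 2: λ = 0.0225 × N × 2/0.5 = 0.09N. The smallest balanced N with 95% power is 148 (power 0.952).
- m = 3: λ = 0.0225 × N × 3/0.5 = 0.135N, giving N = 116 (power 0.950).
- The between-groups test gives 436 (m = 2) or 388 (m = 3).

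So 154 is not the output at exactly f = 0.15. It is the output at f = 0.147 with two measurements, or at f = 0.13 with three. At N = 154 and f = 0.15, power is 95.9% (m = 2) or 98.7% (m = 3).

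**Step 2: dropout.**

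- Participants left: 200 × 0.75 = 150; 200 × 0.70 = 140.
- Needed to keep 154: 154/0.75 = 205.3, so 206 in equal arms; 154/0.70 = 220.
- 154 × 1.30 = 200.2, which suggests that 154 was multiplied up and not divided by the retained fraction.
- 154/200 = 0.77, so 200 tolerates 23% dropout, below both stated figures.

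**Step 3: what f = 0.15 means for the primary comparison.** Let δ be the between-arm difference in mean change and σ the SD at one time point. In a 2 × 2 layout each cell's interaction effect is ±δ/4, so f = δ/(4σ) and δ = 4 × 0.15 × σ = 0.60σ. The SD of a change score is σ√(2(1 − ρ)), which equals σ at ρ = 0.50. The difference is therefore also 0.60 SD of change.

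Check: a two-sample t test on change has noncentrality d²N/4 = 0.36N/4 = 0.09N, the same as in step 1. It also gives N = 148 and power 0.952.

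**Step 4: power at 140 and 150** (two-sided 0.05, ρ = 0.50). The baseline-adjusted columns use residual variance 1 − ρ² = 0.75 of σ².

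| Between-arm difference | Change score, N = 140 | Change score, N = 150 | Baseline-adjusted, N = 140 | Baseline-adjusted, N = 150 |
|---|---|---|---|---|
| 0.60 SD | 94.1% | 95.5% | 98.3% | 98.8% |
| 0.40 SD | 65.2% | 68.2% | 77.4% | 80.2% |
| 0.30 SD | 42.2% | 44.6% | 53.0% | 55.9% |

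**Step 5: detectable difference at 150 and 140.**

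| Analysis | 95% power | 80% power |
|---|---|---|
| Change score | 0.59–0.61 SD | 0.46–0.48 SD |
| Baseline-adjusted | 0.51–0.53 SD | 0.40–0.41 SD |

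**Sensitivity to three measurements.** If three times were entered, f = 0.15 no longer fixes the T0–T1 difference. It is about 0.64 SD if the effect is fully present at T1 and held at T2, and about 0.37 SD if it builds linearly to T2.

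**The case against.** The strongest reply is that the plan is right on its own terms. It says f is around 0.15. A value of 0.147 rounds to that and gives 154, and at exactly 0.15 the stated number exceeds the 148 required. Power for the stated f is 95.9% at 154 and still 94.1–95.5% at 140–150. On the usual benchmarks for f (0.10 small, 0.25 medium), 0.15 is small-to-medium. The identity d = 2f, which would turn 0.15 into 0.30 SD, belongs to a one-way between-groups comparison, and the plan never assumes 0.30 SD. The 0.60 SD figure depends on two measurements, which the section does not state.

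Much of this stands. A reader might infer that the 95% power figure is wrong, or that 154 is an arithmetic error to be replaced by 148. The document supports neither: the power is met, or very nearly met, for the f that was stated, and 154 may be the correct output of an unrounded f. Nor does the document say that a null result would rule out a smaller benefit. That is a risk of misreading.

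The reply leaves two things unanswered. The f benchmarks do not carry over to an interaction f that is then combined with the number of measurements and the correlation, so for the T0–T1 comparison the label understates the difference in SD units. And 140–150 is below 154, whichever f produced it.

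**Conclusion.** The point holds in limited form. On the plan's own dropout, 200 randomised gives 140–150 participants, which is 4–14 short of the stated 154, and the two sections do not agree on the dropout figure. The cost in power is small: at worst 94.1% for f = 0.15 with two measurements.

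The larger matter is interpretation. For the two-arm T0–T1 primary comparison, power of roughly 95% applies to a 0.60 SD difference in FES-I change. For 0.30 SD it is 42–45% on change scores, or 53–56% if baseline-adjusted.

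This rests on two groups, two measurements, correlation 0.50 and epsilon 1. It also assumes that the dropout allowance covers participants excluded for non-adherence; if it does not, the analysed number is lower. Whether 0.60 SD is a realistic expectation cannot be judged here, because the cited intervention studies are not available. It would go too far to conclude that the trial is too small.

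**What to change.** In Sample size {14}:

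- Name the F test, the number of groups, the number of measurements and the unrounded f behind 154.
- Replace the small-to-medium label with the between-arm difference, in SD or FES-I points, for which the trial is powered.
- State that 200 randomised is expected to yield 140–150 participants, and give the detectable difference there for whichever analysis is planned: 0.59–0.61 SD (95% power) and 0.46–0.48 SD (80%) on change scores, or 0.51–0.53 SD and 0.40–0.41 SD if baseline-adjusted at correlation 0.50.

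Use one dropout figure in Sample size {14} and in the section on non-adherence and missing data {20c}, and say whether it includes participants excluded for non-adherence.

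The cost is a few sentences and no extra participants. The drawback for the sponsor is that the stated power will look less favourable.

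### Randomising 200 leaves 150–140 participants at the stated 25–30% drop-out, not the 154 that the plan requires; the effect on power is small

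*Protocol article*

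**What the plan says.** All the figures are in the protocol article.

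- **Sample size {14}, CaF calculation.** From f = 0.15, power 0.95, alpha 0.05, correlation 0.50 and epsilon 1, the text concludes: "This indicates that *n* = 154 participants will need to be enrolled to achieve a successful reduction of CaF".
- **Same paragraph, allowance for loss.** "Based on a drop-out rate of about 25–30% [56], *n* = 200 participants need to be randomly assigned to a group" ("i.e., *n* = 100 per group").
- **Sample size {14}, closing argument.** After the correlation and regression targets (63 and 75), it concludes that a "sample size enrolling *n* = 200 participants with a drop-out of 25–30% will yield a sufficient final participant number", both for reducing CaF and for finding the associations.
- **Handling of non-adherence and missing data {20c}.** Only participants who attend at least 15 sessions (75%) are analysed, and the justification is: "A drop-out rate of 25% was considered in the power calculation; therefore, per-protocol analysis will be conducted".

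**The concern.** The required number, the loss rate, the number randomised and the conclusion of sufficiency are all printed, and they do not fit together. Because 154 is computed before the loss allowance is applied, it has to be the number left for analysis. The per-protocol rule in {20c} reinforces this: the analysed set is what remains after losses, and no larger set is planned that could make up the gap. The two sections also give different loss rates, about 25–30% in {14} and 25% in {20c}. At stake are the accuracy of the sample size justification for the primary outcome and whether the stated power of 0.95 survives the loss that the plan expects.

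**Working it through.** **Inputs.** Required N = 154, randomised N = 200, loss d = 25–30%, f = 0.15, rho = 0.50, epsilon = 1, alpha = 0.05 and power 0.95 (all Sample size {14}); loss of 25% ({20c}); two groups, 1:1 (Trial design {8}). The number of repeated measurements used in the calculation is not stated. Both 2 (T0, T1) and 3 (T0, T1, T2) are shown below as assumptions.

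**1. How 154 becomes 200.** The step is not shown.
- 154 × 1.30 = 200.2, which matches 200.
- 154 × 1.25 = 192.5, which does not.
- 154 / 0.75 = 205.3, so 206 (103 per group).
- 154 / 0.70 = 220 (110 per group).

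The stated 200 is consistent with multiplying by 1.3. It could also be 205 rounded down to a round 100 per group.

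**2. What 200 leaves, N × (1 − d).**
- 200 × 0.75 = 150, which is 4 short of 154.
- 200 × 0.70 = 140, which is 14 short.
- Largest loss that still leaves 154: 1 − 154/200 = 0.23.

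No loss rate in the stated range leaves 154. The association targets of 63 and 75 are met at both 150 and 140.

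**3. Power at those numbers.** This uses the within-between interaction F test for k = 2 groups and m measurements, with noncentrality f² × N × m / (1 − rho) and degrees of freedom (k − 1)(m − 1) and (N − k)(m − 1). For example, at m = 2 and N = 150 the noncentrality is 0.0225 × 150 × 2 / 0.5 = 13.5; at N = 140 it is 12.6.

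| Analysed N | Power, m = 2 | Power, m = 3 |
|---|---|---|
| 154 | 95.9% | 98.7% |
| 150 | 95.5% | 98.5% |
| 140 | 94.1% | 97.9% |

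**4. Check on 154 itself.** With these inputs the interaction test needs 148 at m = 2 and 116 at m = 3, so 154 is not exactly reproduced. A between-group test would need 436 or 388, so it is not the source of 154. The shortfall in step 2 takes 154 as printed. Since 148 already gives 0.95 at m = 2, power at 150 stays above 0.95.

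**The case against.** The strongest reply is that nothing material follows. At the plan's own effect size, 150 participants still give more than 0.95 power, 140 give 94.1% in the less favourable of the two cases, and with three measurements power is well above target. That reply stands, and it limits the point to a mismatch between printed figures. It does not remove the mismatch: the sufficiency sentence is tied to 154, and 150–140 is below 154.

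Four stronger readings are tempting, and the documents do not support them.

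- **The trial is underpowered.** Taking 154 as exactly the 95% number and solving backwards gives f = 0.1462, with power of 94.5% at 150 and 93.0% at 140. That effect size appears nowhere in the plan, which states f = 0.15.
- **The error is a multiplication by 1.3.** It fits closely, but the step is not shown, and with a rate described only as approximate, rounding down from 205 is also possible. The shortfall does not depend on the cause.
- **No allowance was made for attendance exclusions, so the gap is larger.** {20c} links its 25% allowance directly to the per-protocol analysis, so the allowance may already cover them. If it did not, and if a further 10% of completers were excluded (an assumption), 150 × 0.9 = 135 and 140 × 0.9 = 126 would remain, with power of 93.3% and 91.6% at f = 0.15 and two measurements. This shows why the text should be clear; it does not show a larger shortfall.
- **The two loss rates contradict each other.** 25% is the lower end of about 25–30%. This is loose wording, but a single figure is needed to know what was planned.

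**Conclusion.** The point holds as a minor inconsistency. With 200 randomised and 25–30% loss, 150–140 are analysed, 4 to 14 fewer than the 154 that the plan says it needs, and the claim of sufficiency for the CaF outcome does not match that figure anywhere in the stated range. Power is at most about one percentage point below 0.95.

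The shortfall rests only on printed numbers. The power statement rests on f = 0.15, rho = 0.50, the within-between interaction test, two or three measurements, and the stated loss including the attendance exclusions. Neither the design nor the choice of analysis has to change.

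**What to change.** Leave enrolment at 200 and correct the text.

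1. In Sample size {14}, both where 200 is derived and in the closing sufficiency sentence, write for example: *200 randomised retains 154 if loss is at most 23%; at 25–30% loss, 150–140 are analysed.*
2. Give the power at 150 and 140 from the authors' own G*Power settings, naming the test and the number of measurements. At f = 0.15 and rho = 0.50, the figures to expect are about 95.5–94.1% with two measurements and about 98.5–97.9% with three.
3. Keep the statement that the targets of 63 and 75 are met, but separate it from the statement about CaF.
4. Use the same drop-out figure in {14} and {20c}, and state whether it includes participants excluded under the attendance rule.

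The cost is a few sentences and one rerun of the existing power calculation. With two measurements, the power reported at 30% loss would be slightly below 0.95.

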### Objectives {7}

The main and overarching objective of the project is to understand the role of the psychobiological stress response, including stress system alterations and inflammation, in the vicious cycle between CaF, declines in mobility, and development of muscle loss and sarcopenia. Therefore, a well-established intervention aimed at reducing CaF and increasing activity will be performed, to test whether a reduction of CaF can break the vicious cycle, and stop the downward spiral towards sarcopenia.

The specific objectives of the study are described in the following:*Objective 1*: To test whether CaF in older adults are positively related with altered stress system activity, specifically overactivity of the sympathetic nervous system (SNS) and hypoactivity of the hypothalamus–pituitary–adrenal (HPA) axis, and higher levels of systemic low-grade inflammation. It will additionally be tested whether general psychological symptoms (stress, anxiety, depression) are similarly or more strongly associated with stress system activity.*Objective 2*: To test whether a well-established CaF-reduction and exercise program reduce CaF will differentially affect stress system activity and reduce or slow down systemic low-grade inflammation. It will additionally be tested if and how general psychological symptoms (stress, anxiety, depression) are affected by the intervention.*Objective 3*: To test for directionality of the brain-to-immune/immune-to-brain feedback system by investigating whether reduced CaF precede reductions in inflammation (or lower rate of increase) or whether reductions in inflammation precede reductions in CaF (or lower rate of increase) (or both). It will additionally be tested whether general psychological symptoms (stress, anxiety, depression) provide an alternative or additional pathway.*Objective 4*: To test whether higher inflammation at baseline is predictive of lower success in the intervention group.*Objective 5*: To test whether systemic and intracellular inflammation at T0 is associated with lower decreases of CaF from T0 to T1 and T0 to T2.

This project has been preregistered before the start of data evaluation; see osf.io/m84hq.

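### The adherence-only analysis rule, read literally, also covers the baseline (T0) associations of Objective 1, which need no attendance; those analyses should use all T0 data

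*Protocol article*

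**What the plan says.** Objective 1, in Objectives {7}, is an association question: "To test whether CaF in older adults are positively related with altered stress system activity", and with higher systemic inflammation. It compares no arms and names no time point.

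The second part of Sample size {14} asks whether the planned sample is "sufficient to detect the hypothesized cross-sectional and prospective associations of CaF with stress system activity and inflammation". The figure used is a cross-sectional correlation of FES-I with IL-6, r = 0.4, said to need n = 63, or n = 75 in a regression with up to six predictors. The section concludes that 200 enrolled, less 25–30%, "will yield a sufficient final participant number to not only successfully reduce CaF but also to find the hypothesized associations".

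Section {20c} then sets the analysis population: "Statistical analysis will be conducted with participants who adhere to the intervention, while non-adherent participants will be excluded from the analysis". Adherent means at least 15 sessions (75%). The reason given is that 25% drop-out had been allowed for in the power calculation. No section exempts the baseline associations.

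Implementation {16c} places the baseline assessments before randomisation, and therefore before any session.

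**The concern.** A correlation between FES-I and a biomarker at T0 is fully observed before anyone can adhere or drop out. Applying an attendance rule to it has two consequences.

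- **Lost precision.** Valid baseline records are set aside for a reason unrelated to the question.
- **Selection on a later event.** If attendance depends on both CaF and inflammation, the correlation among attenders can differ from that in the enrolled sample. The protocol gives grounds to take this seriously: its background links CaF to avoiding activity and inflammation to frailty, and Objective 4 tests whether higher baseline inflammation predicts less success in the intervention group.

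This is separate from the choice of analysis set for the arm comparison. A change confined to the primary outcome would leave the associations counted on the reduced number.

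**Working it through.** **Inputs.** n = 200, drop-out 25–30%, r = 0.4, power 0.95 and alpha 0.05 (sidedness not stated), all from {14}; the attendance rule from {20c}.

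**1. The plan's own figure.** Fisher z: n = ((z_alpha + z_power) / atanh(r))² + 3, with atanh(0.4) = 0.4236.

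- One-sided: ((1.645 + 1.645) / 0.4236)² + 3 = 63.3, which reproduces 63.
- Two-sided: ((1.960 + 1.645) / 0.4236)² + 3 = 75.4.

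So the stated 63 is a one-sided figure.

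**2. Records affected.** 200 × 0.25 = 50 and 200 × 0.30 = 60, leaving 150 and 140. This is an allowance, not a count. Section {20c} cites only 25% and treats drop-out and non-adherence as one quantity.

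**3. Precision.** The standard error of Fisher z is 1/√(n − 3).

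- n = 150 against 200: √(197/147) = 1.158, about 16% larger.
- n = 140 against 200: √(197/137) = 1.199, about 20% larger.

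**4. Power at the protocol's effect, and the detectable r.** Power = Φ(atanh(r)·√(n − 3) − z_alpha). Detectable r = tanh((z_alpha + z_power)/√(n − 3)).

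| n | Power at r = 0.4, two-sided | r detectable at 95% power, two-sided | r detectable at 95% power, one-sided |
|---|---|---|---|
| 140 | 0.999 | 0.299 | 0.274 |
| 150 | 0.999 | 0.289 | 0.265 |
| 200 | above 0.999 | 0.251 | 0.230 |

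Both 140 and 150 exceed the stated requirements of 63 and 75. The loss matters only if the true correlation is well below 0.4. At an assumed r = 0.2, two-sided power is 0.66, 0.69 and 0.81 at n = 140, 150 and 200.

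**5. Selection, by assumption only.** The document gives no relation between attendance and FES-I or IL-6. I simulated bivariate normal variables (2,000,000 draws) with logistic retention of 70–75% and the same absolute log-odds per SD for each variable.

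| Assumed retention pattern | True r = 0 becomes | True r = 0.40 becomes |
|---|---|---|
| Falls with both, log-odds 0.3 per SD | about −0.02 | 0.38 |
| Falls with both, log-odds 0.8 per SD | −0.08 to −0.09 | 0.30 to 0.31 |
| Rises with CaF, falls with IL-6, 0.3 per SD | about +0.02 | 0.41 |
| Rises with CaF, falls with IL-6, 0.8 per SD | +0.08 to +0.09 | 0.45 |
| Depends on IL-6 only, 0.7 per SD | 0.00 | 0.39 |

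Both the sign and the size change with the assumption.

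**The case against.** Four objections carry weight.

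- **The rule may not be meant for Objective 1.** Section {20c} is about non-adherence to the intervention and ends in per-protocol language that fits an arm comparison. Objective 1 names no time point, whereas Objectives 4 and 5 do, and measurements are also taken at T1 and T2. This stands as a caution: T0 is the natural reading of cross-sectional, not a stated fact. But the exclusion is worded without limit, and {14} counts the reduced number for the same associations, so the literal reading is the one an analyst would follow.
- **The sufficiency statement is not wrong.** This stands in full. A reader might infer that the restriction leaves Objective 1 underpowered. At r = 0.4 it does not. The number after drop-out is a safe floor for sizing, and using it there does not by itself commit anyone to discarding T0 data; {20c} does that.
- **The bias is conjectural.** Also right. A reader might infer that the correlation will be pulled down, against the hypothesis. That needs attendance to fall with both variables, which nothing in the document establishes; opposite-signed dependence inflates it.
- **Fifty to sixty valid records overstates the loss.** Partly right. It is a planning allowance. Saliva samples are collected at home and posted, and {11c} anticipates some not being returned, so 200 is an upper limit for cortisol and alpha-amylase.

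The further argument that analysis sets are commonly left to a fuller plan does not dispose of the point, because the article does fix a set, and it is a poor one for this objective.

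**Conclusion.** The concern holds in limited form. As written, the adherence rule reaches a baseline association that needs neither attendance nor follow-up. The cost is up to 50–60 of 200 T0 records on the protocol's allowance, a Fisher-z standard error about 16–20% larger, and conditioning on a later event whose effect on the estimate is unknown in size and sign. It is not a power failure at the planned effect, and no figure in {14} has to be corrected on this account. The conclusion rests on reading the cross-sectional part of Objective 1 as T0, on taking the unqualified exclusion literally, and on using the drop-out allowance as the expected loss. It does not affect the primary outcome.

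**What to change.** In {20c}, add that the cross-sectional (T0) analyses of Objective 1 use every randomised participant with valid T0 data for the variables concerned, whatever their later attendance or drop-out, and that the adherence-based set does not apply to them.

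The sufficiency sentence in {14} can stay; the reduced number remains relevant to associations that need T1 or T2. If a detectable correlation is added for the T0 analyses, give its sidedness, because the existing n = 63 is one-sided: at 95% power and n = 200 it is about 0.25 two-sided or 0.23 one-sided.

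Cost: one sentence, with no new data, visits or burden on participants.
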